## Abstract

**Background:**

One in four Canadian families struggle with infant sleep disturbances. The aim of this study is to evaluate Play2Sleep in families of infants with sleep disturbances. In addition to parental education on infant sleep, Play2Sleep uses examples from a video-recorded, structured play session with mothers and fathers separately to provide feedback on parent–infant interactions and their infant’s sleep-related social cues. The quantitative phase will answer the research question: Does one dose of Play2Sleep delivered during a home visit with mothers and fathers of infants aged 5 months reduce night wakings at age 7 months? The qualitative phase will answer the research question: What are parental perceptions of family experiences, processes, and contexts related to Play2Sleep and infant sleep? The overarching mixed methods research question is as follows: How do parental perceptions of family experiences, processes, and contexts related to infant sleep explain the effectiveness of Play2Sleep?

**Method and analysis:**

An explanatory sequential mixed methods design will be used. In the quantitative phase, a randomized controlled trial and RM-ANOVA will compare night wakings in infants whose parents receive Play2Sleep versus standard public health nursing information. Sixty English-speaking families (mothers and fathers) of full-term, healthy, singleton, 5-month-old infants who perceive that their infant has sleep disturbances will be recruited. The primary outcome measure will be change in the number of night wakings reported by parents. The qualitative component will use thematic analysis of family interviews to describe parental perceptions and experiences of infant sleep. Mixed methods integration will use qualitative findings to explain quantitative results.

**Discussion:**

Play2Sleep is a novel approach that combines information about infant sleep with personalized feedback on parent–infant interactions and infant cues. Including fathers and mixed methods should capture complex family experiences of infant sleep disturbances and Play2Sleep. If effective, Play2Sleep has possible application for preventing infant sleep disturbance and tailoring for other populations.

**Clinical Trial Registration:**

www.ClinicalTrials.gov, identifier: NCT02742155. Registered on 2016 April 23.

## Introduction

Approximately one in four Canadian families experience infant sleep disturbances (1). Infant sleep disturbances are associated with parental feelings of guilt and helplessness, as well as maternal depression and anxiety (2–5). Parents may bed-share with their infants in response to infant sleep disturbances despite awareness of safe sleep recommendations that discourage this practice (6, 7). Furthermore, infant sleep disturbances are associated with increased infant stress hormones (8) and may predict socio-emotional difficulties (9). Assisting families in managing infant sleep disturbances may improve family health, as well as support child development. Time constraints and lack of provider confidence in being able to address sleep concerns may hinder primary health care providers’ ability to address sleep concerns during primary care visits (10). The proliferation of privatized and unregulated sleep consultants (11) highlights a noteworthy gap in Canada’s public health care system.

In a Cochrane review of postnatal parental education, parental education was shown to be effective in improving the amount of nighttime infant sleep duration by 29 min; however, similar improvements in infant crying were not observed (12). Other individual trials provide further evidence that parental education on infant sleep can be an effective means for changing sleep-related parenting practices (13) and improving infant nighttime sleep consolidation while decreasing parental perception of night waking severity (14). Behavioral-based sleep interventions improve sleep in over 80% of children under age 5 years (15). Yet, in a Canadian community-based survey, less than half of parents reported they were able to successfully manage their infant’s sleep disturbances using behavioral-based sleep strategies (16). Furthermore, parents may experience reservations and practical challenges when applying behavioral-based approaches (17, 18). Moreover, despite evidence that higher father engagement may mitigate maternal stress associated with infant sleep disturbances (19) and reduce infant night wakings (20), including fathers in infant sleep intervention research is limited.

Addressing only sleep-related parenting behaviors and interactions may be ineffective in improving broader parenting difficulties that may underlie infant sleep disturbances (21, 22). When examining links between maternal sensitivity and infant sleep, researchers have found that maternal sensitivity was positively linked to subsequent, but not concurrent (23), sleep consolidation (24, 25). Mothers observed to be more sensitive during an unstructured play session, according to the adult sensitivity scale of the Child–Adult Relationship Experimental Index, reported better perceived sleep quality in their 7- to 18-month-old infants (26). However, parent–child interactions are influenced by more than only maternal sensitivity and it may be important to recognize the dyadic nature of parent–child interactions. For instance, Scher (23) found that infants who were highly responsive in play interactions had more frequent night wakings than infants who were not as responsive. Some researchers have instead examined how infant sleep may be related to emotional availability, a dyadic concept that considers the emotional quality of parent–child interactions and includes sensitivity. Findings from these researchers demonstrate a positive association between greater emotional availability at bedtime and fewer night wakings (27) and more rapid increases in the amount of nighttime sleep during the first 6 months of life (28).

Treyvaud and colleagues (29) found mothers who reported poorer sleep quality themselves were observed to have greater difficulty recognizing and responding to their infant’s subtle and potent social cues. Over the duration of a 5-day residential parenting program, this sample of mothers was observed to have improvements in overall parent–child interactions, including contingent responses, and perceived that their child’s behavior difficulties, 80% of which were related to sleep issues, had decreased in frequency and severity (29). Another intervention with parents of maltreated toddlers aimed at improving the parent–child relationship by promoting responsive care using a series of video feedback sessions resulted in a reduction in sleep disturbances (30). However, researchers have not examined this relational approach in an otherwise healthy community-based population experiencing sleep disturbances. Thus, promoting positive parent–child interactions in a manner that enhances parental ability to identify infant sleep-related social cues represents a novel strategy that could be used to complement educational approaches to more effectively support families challenged with infant sleep disturbances.

Parent–child interactions influence the architecture of children’s growing brains, as well as developmental outcomes (31, 32). High quality parent–child interactions occur with sensitive and effective parental behaviors that are contingent upon the child’s clear and responsive verbal and non-verbal communication cues (33, 34). Parent coaching can improve the quality of parent–child interactions. This type of coaching is closely aligned with the skill set of registered nurses, such as expertise in relational communication, knowledge of healthy early childhood development, and proficiency in strengths-based approaches (35, 36). Providing personalized feedback on self-modeled, video-recorded, structured parent–infant interactions is a feasible and effective strategy for improving parental interactions with preterm and term infants (37–40).

The proposed nursing theory described by [name] and [name] (41) forms the theoretical underpinnings of this study. Informed by Bronfenbrenner’s ecological theory (42, 43) and Barnard’s Model of parent–child interactions (44), [name] and [name] guide nurses to consider parental knowledge and beliefs about infant sleep with the family’s synchrony, not only relating to sleep but also the family’s ability to engage in effective parent–infant interactions. As such, nurses are encouraged to enhance parental knowledge related to infant sleep, as well as the underlying foundational familial interactions that support parental ability to apply knowledge relating to infant sleep during daily and foundational parent–infant interactions. Play2Sleep is an intervention that uses personalized feedback of structured parent–infant play sessions. This approach could help address broader parenting difficulties that may underlie infant sleep disturbances by enhancing parental ability to identify and respond appropriately to their infant’s specific sleep-related and social cues. This study extends previous self-modeled, video-recorded interaction guidance interventions and aims to evaluate Play2Sleep to improve infant sleep. This protocol was prepared in accordance with the SPIRIT guidelines (45), as well as the TIDieR checklist and guide (46) for reporting of interventions.

The overarching mixed methods research aim is to understand how parental perceptions of family experiences, processes, and contexts related to infant sleep explain the effectiveness of Play2Sleep. The objective of the quantitative phase is to compare the effect on infant sleep of one dose of Play2Sleep delivered during home visits with mothers and fathers of 5-month-old infants with sleep disturbances against standard infant sleep education only. The primary hypothesis is that Play2Sleep will decrease the number of night wakings at the age of 7 months. The objective of the qualitative phase is to describe parental perceptions of family experiences, processes, and contexts related to Play2Sleep and infant sleep.

## Materials and Equipment

### Study Design

This study will employ a mixed methods, explanatory sequential design to evaluate the Play2Sleep intervention, with priority given to the quantitative phase (Figure 1). Phase 1 is a single center, prospective, randomized, controlled, parallel group, two arm, superiority trial with a 1:1 allocation ratio (ClinicalTrials.gov, identifier NCT02742155). Baseline data collection and intervention will occur when the infant is 5 months of age (±2 weeks), with outcomes measured when the infant is 7 months of age (±2 weeks). During Phase 2, interviews will be conducted with a subset of participating families (mothers and fathers together) about their perceptions and experiences related to their infant’s sleep. The interviews will occur after the outcome home visit takes place, and analyzed using thematic analysis. Phase 3, the integration phase, will focus on explaining the quantitative results from Phase 1 using the qualitative findings from Phase 2.

**Figure 1 F1:**
[figure not shown]
Flow chart of the study.

#### Rationale for Study Design

Researchers are increasingly using qualitative research to facilitate the interpretation of randomized controlled trial findings (47). The quantitative phase will provide evidence relating to the measurable impact of Play2Sleep, while the qualitative phase will provide crucial information that will contextualize the outcomes of Play2Sleep and increase understanding of the processes that contribute to its effectiveness. The integration of qualitative and quantitative findings will be used to explain the measureable impact of Play2Sleep using perceptions and experiences described by parents.

### Participants

The study will take place in a large urban center in Western Canada (Calgary, AB, Canada). Public health nurses will introduce potential participants to the study during 4-month well-baby clinics at eight urban-zone local community health centers. In addition to recruitment posters and postcards placed at each of the community health centers, researchers will use a social media campaign to promote the study on Facebook and Kijiji. At the community health centers, interested families will receive a card with a brief description of the study and public health nurses will request written permission from the parents to be contacted by the researcher. Upon contact with interested families, the researcher will follow a telephone script to (1) screen parents for eligibility, (2) obtain verbal consent from both parents to participate, (3) collect contact information, and (4) schedule the first home visit. Parents who are ineligible for the study will be offered standard public health information on infant sleep and provided with a list of community resources to which they can self-refer.

Participants (mothers and fathers) will be eligible if they meet the following inclusion criteria: (1) are cohabiting mothers and fathers of full-term, healthy, singleton, 4-month-old infants; (2) are first-time parents; (3) are able to read, write, and speak English; (4) perceive that their infant has sleep disturbances; (5) have an infant who has greater than 3 night wakings per night and/or is awake greater than 60 min during the night, and/or has less than 9 h total day and nighttime sleep. Infants meeting one or more of these three objective sleep criteria were considered to be poor sleepers by Sadeh (48) in the development of the original Brief Infant Sleep Questionnaire (BISQ). Participants will be excluded if there is a known or suspected medical or physiological cause of sleep disturbance in either parent or their infant.

### Sample Size

The effect size for the sample size calculation for the quantitative phase was estimated from research that examined brief sleep interventions with the number of night wakings as the primary outcome. A study of a brief internet intervention for families of young children up to age 3 years that provided a customized sleep program, with and without a standardized bedtime routine, found relatively large effect sizes (partial eta squared) of 0.442 and 0.441, respectively (49). In a narrower age group of infants 6–12 months, Hall and colleagues (50) found an effect size (Cohen’s *d*) of 0.64 for an intervention that included a 2-h teaching session and telephone support for parents. An *a priori* analysis was conducted in G*Power for repeated measures ANOVA, between factors (51). This calculation determined that a total sample size of 60 mother–father–infant triads (30 families in each group) would detect an effect size of 0.32 with a power of 0.80 at a 0.05 level of significance (Figure 2), which is below the effect size of the aforementioned studies (49, 50). Recruitment will be ongoing until complete data are collected from 60 families. Based on previous studies (37, 39), attrition is estimated to be very low (less than 5%) after the initial home visit. Figure 3 shows the proposed Consolidated Standards of Reporting Trials flow diagram.

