## Anticipated Results

### Phase 1 Quantitative Analysis

Quantitative data will be analyzed using IBM SPSS Statistics 24.0 software. Data will be examined for frequency and patterns of missing data. If less than 20% of the data are missing, and if missing at random or completely at random, missing values will be imputed using multiple imputation (80). Descriptive statistics (means, SDs, frequencies, and percentages) will be used to describe the sample, and correlations between variables will be examined to identify potential covariates. Using the “intent to treat” principle, a RM-ANOVA will be used to detect differences between groups over time in mother and father reports of infant sleep patterns that are measured as continuous variables (night wakings, nocturnal wakefulness, and longest period of consolidated nighttime sleep). To control for Type I error that may result from multiple hypothesis testing, we will apply a Bonferroni correction during the analyses. Ordinal level infant sleep variables (sleep latency and parental perception of problematic sleep) will be analyzed using a Wilcoxon signed-rank test. If there are statistically significant differences between groups on the primary outcome, sub-analyses will identify which covariates have significant effects. Parent–child interactions scores for both mothers and fathers will be compared to normed scores available from the NCAST database.

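### The stated 0.80 power was calculated for the group main effect, so it is not established for the group-by-time (change) comparison that the trial makes primary

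*Protocol article*

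**What the plan says.** **Sizing.** The protocol article, Sample Size, says the "analysis was conducted in G*Power for repeated measures ANOVA, between factors". The section puts the size at 60 families, split equally between the arms, and claims that this number "would detect an effect size of 0.32 with a power of 0.80 at a 0.05 level of significance". The metric of the 0.32 is not named. Among the studies cited in support, the one in infants aged 6–12 months "found an effect size (Cohen’s *d*) of 0.64 for an intervention that included a 2-h teaching session and telephone support for parents".

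**Test.** The Abstract says: "The primary outcome measure will be change in the number of night wakings reported by parents". The Introduction says: "The primary hypothesis is that Play2Sleep will decrease the number of night wakings at the age of 7 months". Under Phase 1 Quantitative Analysis, "a RM-ANOVA will be used to detect differences between groups over time in mother and father reports of infant sleep patterns".

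**Timing.** Data Collection and Management gives two measurement times, 5 and 7 months. The randomisation code is requested only after the parents have completed the baseline questionnaire.

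**The concern.** In G*Power, the between-factors option for repeated measures sizes the comparison of group means averaged over the repeated measurements. If those measurements are baseline and 7 months, half of the average is taken before anyone is allocated, and the expected arm difference there is zero. A 7-month difference of d then enters the average as d/2.

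The comparison that the Abstract and the Phase 1 analysis make primary is the group-by-time term, that is, the arm difference in change. Its precision depends on the baseline-to-outcome correlation in the opposite direction: a higher correlation helps the change comparison and hurts the average. Power for one term therefore cannot be carried over to the other.

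At stake is the only power justification given for the primary hypothesis. There is also ambiguity about which line of the RM-ANOVA output is the trial's result, because the Sample Size section points to one term and the outcome definition to another.

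**Working it through.** **Inputs from the protocol article.** N = 60 (30 per arm), effect size 0.32, power 0.80, alpha 0.05 and the between-factors option (Sample Size); m = 2 times, with baseline before allocation (Data Collection and Management); cited d = 0.64 (Sample Size).

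**Assumptions.** 0.32 is Cohen's f, the metric G*Power uses for this test. Rho is not in the visible text, so a range is shown. The cited d is taken as the 7-month difference in SD units. All tests are noncentral F with 1 numerator df.

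**Step 1: reproduce the stated figure.** Between factors, λ = f²·N·m / (1 + (m−1)·rho), with denominator df N−2.
- At rho = 0.5: λ = 0.1024 × 60 × 2 / 1.5 = 8.19, power 0.804, and the smallest N for 0.80 is 60. The stated figure is reproduced.
- At rho = 0.3 the required N is 52; at rho = 0.7 it is 68.

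**Step 2: could the option label be a slip?** For the within-between interaction, λ = f²·N·m / (1−rho). With f = 0.32, the required N is 42 / 30 / 22 / 14 at rho = 0 / 0.3 / 0.5 / 0.7. None of these gives 60, so the label and the number agree with each other.

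**Step 3: what the sized effect implies at 7 months.** For two equal groups f = d/2, so f = 0.32 is an averaged difference of 0.64 SD. With no difference at baseline, that average needs 2 × 0.64 = 1.28 SD at 7 months, twice the cited d.

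**Step 4: power of the primary comparison at d = 0.64 and 30 per arm.**
- Group-by-time: the difference in change is d and the SD of change is √(2(1−rho)). So λ = 15·d² / (2(1−rho)) = 15 × 0.4096 / (2(1−rho)) = 3.072 / (1−rho), df 58.
- Baseline-adjusted 7-month difference: λ = 15·d² / (1−rho²) = 6.144 / (1−rho²), df 57.

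| rho | Group-by-time λ | Power | Baseline-adjusted λ | Power |
|---|---|---|---|---|
| 0.3 | 4.39 | 0.54 | 6.75 | 0.72 |
| 0.5 | 6.14 | 0.68 | 8.19 | 0.80 |
| 0.7 | 10.24 | 0.88 | 12.05 | 0.93 |

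A simulation of 20,000 trials at rho = 0.5 gave 0.683 for the change comparison.

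**Step 5: where group-by-time power reaches 0.80.** In Step 1, f = 0.3185 gives exactly 0.80 at N = 60 and rho = 0.5, so the λ needed with df 58 is 0.3185² × 80 = 8.12. Setting 3.072 / (1−rho) = 8.12 gives rho of about 0.62. Put the other way, the 7-month difference detectable with 0.80 power by the change comparison is 0.87 / 0.74 / 0.57 SD at rho = 0.3 / 0.5 / 0.7.

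**The case against.** **The direction of the error is not fixed.** This stands. The value rho = 0.5 is back-fitted from N = 60 and is not unique: four measurements with rho = 0.7 give N = 62, although the article describes two times. Figure 2, the power plot, is not shown and may carry more detail. Table 2 cites a 3-week test–retest reliability of 0.82–0.95 for the sleep questionnaire. Two months of rapid development should lower that, but at rho = 0.8 group-by-time power would be 0.97. A reader might infer that the trial is underpowered; the documents do not support that as a flat statement.

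**The repeated measure might be the two parents' reports.** The Sample Size section does not say what was entered. If it was mother and father reports of change, or of the 7-month value, the between-factors option would be right and there would be no dilution by baseline. This is not excluded. It is less likely, because the analysis section describes differences over time and the outcome is change.

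**The effect size is open.** The other cited study reports partial eta squared of 0.442 and 0.441 (f = √(0.442/0.558), about 0.89), far above 0.32. If 0.32 is read as the interaction effect itself, group-by-time power at rho = 0.5 is 0.998. This also stands, but it means a 7-month difference of 1.28 SD, which the article does not state as its target.

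**Power of the main effect.** At d = 0.64 the group main effect would have power of only 0.33 / 0.29 / 0.26 at rho = 0.3 / 0.5 / 0.7. A reader might infer that the trial's result will have power this low. The analysis section does not plan that test as the primary comparison, so these figures are a reason to name the contrast and not a measure of harm.

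**The full plan may settle it.** The point does not rest on an omission. The article names a sizing procedure that does not match its own outcome and analysis.

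**Conclusion.** The concern holds as a mismatch between the sizing and the test. It is not an arithmetic slip, since the calculation is correct for the option named. With time as the repeated factor, the 0.80 applies to a contrast that mixes pre-randomisation baseline with 7 months, and the article does not establish it for the change comparison. Taking d = 0.64 as the 7-month difference, the planned comparison falls short at the rho that reproduces the sample size (0.68) and exceeds 0.80 only above a rho of about 0.62. The conclusion is that 0.80 is not established, not that power is inadequate. Severity is moderate: the primary contrast and its power statement need correcting, while the number of families need not change.

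**What to change.** Before analysis, state that the primary contrast is the group-by-time term or, preferably, the 7-month arm difference adjusted for the baseline value already collected, and that it is not the group main effect. Restate the power of 60 families for that contrast, giving the assumed 7-month difference and rho, and say what the repeated measure is and how the two parents' reports enter. The baseline-adjusted option is preferred because it has the higher power at every rho tabulated and meets 0.80 at d = 0.64 and rho = 0.5 with the same 60 families. Restating power for the group-by-time term alone would also resolve the inconsistency.

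The cost is a recalculation and a few sentences. The article reports 54 triads already enrolled and expects to need 61 for 60 complete; neither figure has to change. The downside is that the stated power may become less favourable.

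### The detectable effect of 0.32 is a Cohen's f, nominally d = 0.64, so it is not below the d of 0.64 cited from reference 50

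*Protocol article*

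**What the plan says.** The Sample Size section of the protocol article draws its effect size from two earlier studies of brief sleep interventions. For the internet study (reference 49) it reports that the authors "found relatively large effect sizes (partial eta squared) of 0.442 and 0.441, respectively (49". For the study in infants of 6 to 12 months (reference 50) it reports that they "found an effect size (Cohen’s *d*) of 0.64 for an intervention that included a 2-h teaching session and telephone support for parents".

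It then names the procedure: "An *a priori* analysis was conducted in G*Power for repeated measures ANOVA, between factors (51". The planned size is 60 families, 30 per arm, and the section's claim for that number is that it "would detect an effect size of 0.32 with a power of 0.80 at a 0.05 level of significance". The sentence closes by placing 0.32 against both sources: "which is below the effect size of the aforementioned studies (49, 50". The text does not say which metric 0.32 is on.

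**The concern.** Partial eta squared, Cohen's d and the G*Power effect size are different scales, and their values cannot be ranked without conversion. The closing comparison is the only argument in the section that 60 families is a cautious choice. It tells the reader that the trial can detect less than either earlier study found. If 0.32 is Cohen's f, that is untrue for reference 50. That study has the narrower infant age range and so lies closer to an outcome at 7 months. Readers of a result without a group difference would then credit the trial with more sensitivity than its own calculation gives it.

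**Working it through.** **Inputs from the protocol article**
- N = 60, 30 per group, power 0.80, alpha 0.05, effect size 0.32, G*Power repeated measures ANOVA, between factors (Sample Size).
- k = 2 groups: "two arm, superiority trial with a 1:1 allocation ratio" (Study Design).
- m = 2 measurements, at 5 and 7 months (Study Design).
- Cited effects: partial eta squared 0.442 and 0.441; d = 0.64 (Sample Size).

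**Assumption.** The article gives no correlation between measurements. I take rho = 0.5 and vary it below.

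**Step 1: reproduce the stated figure with 0.32 as Cohen's f.** The between-factors test uses a noncentral F with lambda = N × f² × m / (1 + (m − 1) × rho), on k − 1 and N − k degrees of freedom.
- lambda = 60 × 0.1024 × 2 / 1.5 = 8.19, df (1, 58): power 0.804.
- N = 58 gives 0.790, so 60 is the smallest even N that reaches 0.80.
- The exact detectable effect at N = 60 is f = 0.3185.

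The stated N and power are reproduced.

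**Step 2: try the other readings of 0.32.**
- As d, f = 0.32 / 2 = 0.16 and lambda = 60 × 0.0256 × 2 / 1.5 = 2.05: power 0.29. With m = 2 it ranges from 0.24 (rho 0.9) to 0.41 (rho 0). With m = 4 (both parents at both times) and rho = 0 it is still only 0.68. At m = 2 and rho = 0.5, power 0.80 would need 232 families.
- As partial eta squared, f = √(0.32 / 0.68) = 0.686: power above 0.999.

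Neither fits the stated figures.

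**Step 3: put every effect on one scale.** For two equal groups d = 2f. Also f = √(η² / (1 − η²)) and η² = f² / (1 + f²).

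| Source | As given | f | d |
|---|---|---|---|
| This trial | 0.32 | 0.32 | 0.64 |
| Reference 50 | d = 0.64 | 0.32 | 0.64 |
| Reference 49 | η² = 0.442 | √(0.442 / 0.558) = 0.890 | 1.78 |
| Reference 49 | η² = 0.441 | √(0.441 / 0.559) = 0.888 | 1.78 |

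The trial's f = 0.32 is partial eta squared 0.1024 / 1.1024 = 0.093. The conversion d = 2f does not involve rho.

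**Step 4: sensitivity to rho (m = 2).** Power for f = 0.32 is 0.88 at rho 0.2, 0.86 at 0.3, 0.80 at 0.5, 0.75 at 0.7 and 0.73 at 0.8. The matching detectable d is 0.57, 0.59, 0.64, 0.68 and 0.70.

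**Step 5: what the between-factors figure means at 7 months.** That test concerns the group difference averaged over the measurements. Randomised groups have no expected difference at baseline. A difference of 0.64 SD at 7 months therefore averages (0 + 0.64) / 2 = 0.32 SD, which is f = 0.16, with power 0.29 from Step 2. A two-sample t-test at 7 months with 30 per arm has noncentrality 0.64 × √(30 / 2) = 2.48 on 58 df, power 0.68. The group-by-time contrast also has 0.68 at rho 0.5 (0.54 at rho 0.3, 0.88 at rho 0.7).

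**The case against.** The fairest defence has four parts.

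1. **The claim is true for one of the two sources.** On a common scale 0.32 lies well below f of about 0.89 for reference 49, provided that study's partial eta squared describes a comparable contrast. This stands. A reader might infer that the trial has no margin against any earlier evidence, but the documents do not support that.

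2. **The article says only that 0.32 is lower.** It does not say that the trial can detect half the earlier effect. This also stands. Power for a half-size effect (0.23 by a t-test at d = 0.32) answers a claim that the article does not make.

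3. **Equality with reference 50 is nominal.** The article does not say whether that d is a follow-up difference, a difference in change or a within-group change, and it does not describe that study's control arm. A reader might infer that the trial is sized for exactly that intervention's effect, or that the effect here must be smaller because both arms receive sleep education. Neither can be settled from the article. What can be settled is that the two numbers coincide after conversion, so 0.32 cannot be called the lower one.

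4. **The metric may be labelled in Figure 2, which is not shown, and rho = 0.5 is assumed.** The missing label should therefore not be pressed as an omission. Neither point rescues the comparison: the article fixes 0.32 itself, and d = 2f holds whatever rho is.

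**Conclusion.** The comparison is wrong as written for reference 50 and correct for reference 49. Under the procedure the article names, N = 60 and power 0.80 reproduce with 0.32 as Cohen's f (0.804) and not as d (0.29). As f it is nominally d = 0.64, the figure cited for reference 50. The reproduction rests on m = 2 and an assumed rho of 0.5. The conversion rests only on two equal groups.

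The calculation itself is not in error: 60 families do give power 0.80 for f = 0.32 under those assumptions. What fails is the stated advantage over the closer of the two earlier studies. It would be a second mistake to correct the sentence into a claim of 80% power for d = 0.64 at 7 months. On the simplest analysis of that time point, power is about 0.68.

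**What to change.** Revise the end of the Sample Size section to:
- name 0.32 as Cohen's f and give its equivalents (nominal d = 0.64, partial eta squared about 0.093);
- give the cited effects on the same scale (f about 0.89 for reference 49, f = 0.32 for reference 50);
- keep the statement that the detectable effect is lower for reference 49 only, and withdraw it for reference 50;
- state the number of measurements and the correlation entered in G*Power (0.5 is inferred here, so the value actually used should be reported);
- say that the effect is a group difference averaged over the measurements, and that it is not 80% power for d = 0.64 at 7 months (about 0.68 by a two-sample t-test with 30 per arm).

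The cost is a text change. Enrolment, reported as 54 families with 61 expected, is unaffected. The downside is that the stated sensitivity becomes less favourable.
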